## Primary Safety Endpoints

1. Clinically significant Hypercalceamia

This is the most likely safety issue to occur during the trial. Previous studies (28,29) have demonstrated that our proposed dose regimen is very unlikely to cause hypercalcaemia while providing an effective increase in vitamin D levels. Furthermore, it has been reported that vitamin D supplementation as per current guidelines is extremely unlikely to cause hypervitaminosis D and that the toxic effects of vitamin D (hypercalcemia) only start to occur at levels > 200 nmol/L, well above the expected vitamin D level for the dose regimen proposed in this study (31,32).

# Subject Selection and Withdrawal

## Inclusion Criteria

1. eGFR between 15 and 60 ml/min/1.73m2
2. Serum 25 (OH) vitamin D levels <40nmol/L as measured within the last 2 months
3. No evidence of diabetes mellitus (fasting blood sugar <7.1, not taking any diabetic medication)
4. Not receiving haemo or peritoneal dialysis
5. No dialysis therapy within the last 3 months
6. Age > 18 years and < 80 years
7. Patient agrees not use any medications (prescribed or over-the-counter including herbal remedies) judged to be clinically significant by the Principal Investigator during the course of the study.
8. Able to understand and sign the written Informed Consent Form.
9. Able and willing to follow the Protocol requirements.

## Exclusion Criteria

# 1. Currently receiving oral ergocalciferol at any dose

# 2. Received IM ergocalciferol therapy within last 3 months

# 3. Receiving renal replacement therapy of any type or having recently received any form of dialysis (within 3 months)

# 4. Pacemaker or any other implanted cardiac device

# 5. Serum calcium above 2.6 mmol/L at screening

# 6. Pregnant or lactating

# 7. Known hypersensitivity to ergocalciferol

8. Patient known to have a condition which predisposes to hypercalcaemia (multiple myeloma, sarcoidosis, other granulomatous disease)

9. Initial blood pressure of >160/100 mmHg

10. History of significant liver disease or cirrhosis

11. Anticipated requirement for dialysis in 6 months

12. Malabsorption, severe chronic diarrhea, or ileostomy

13. Known diagnosis of hypervitaminosis D

14. Known to have diabetes mellitus

15. Known to have renal calculi

16. Known to have systemic sclerosis, Raynaud’s phenomenon or other disease associated with known microcirculatory dysfunction

17. Concurrent participation in any other research study

18. Unwilling or unable to complete study protocol

### Females of childbearing potential and males must be willing to use an effective method of contraception (hormonal or barrier method of birth control; abstinence) from the time consent is signed until 6 weeks after treatment discontinuation.

### Females of childbearing potential must have a negative pregnancy test within 7 days prior to being registered for protocol therapy.

### NOTE: Subjects are considered not of child bearing potential if they are surgically sterile (they have undergone a hysterectomy, bilateral tubal ligation, or bilateral oophorectomy) or they are postmenopausal.

## Subject Recruitment and Screening

The examinations will be carried out in a quiet, stable, draught free environment, Temperature and humidity will be controlled (21±1^o^ C, relative humidity 30-40%). Patients will be instructed to have a light breakfast, avoiding fatty foods, tobacco and caffeine and will be asked to abstain from vigorous exercise from the previous evening onwards. They will be supine for 10 mins during acclimatisation.

**Healthy subjects:**

Healthy volunteers will be recruited by advertisement to staff and students of Queen Mary, University of London and Barts & the London NHS Trust and to the general community, as approved by a National Research Ethics Service (NRES) approved Research Ethics Committee.

Fifteen (15) normal, healthy subjects will be recruited to undergo two microcirculatory assessments to determine reproducibility, coefficient of variance and normal ranges for the assessments described in section 7 (iontophoresis, skin autofluorescence, side stream dark field imaging and pulse wave velocity). They will not receive any pharmacological preparation. A blood test will be taken for both baseline and specialist laboratory assays as described in section 6. Patients will be asked to provide written, informed consent before participating.

**Subjects with CKD:**

Subjects will be recruited by an investigator from general nephrology outpatient clinics at the Royal London Hospital. Patients will be contacted after a clinic visit if they meet inclusion/exclusion criteria and offered the chance to participate in the study. Female patients will be asked to undergo a pregnancy test at the time of the initial screening.

Patients will be provided with a full explanation of the nature, purpose and requirements of the study including Patient Information Sheets and Consent Forms. They will be invited to participate in a screening evaluation, which will include a medical history and physical examination. The subject’s General Practitioners will be informed of an individual’s agreement to participate. Results of the screening evaluation will determine eligibility for entry into the study. Patients will have the opportunity to discuss the trial further with an investigator before giving consent.

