# Study Procedures and Schedule of Assessments

Patients will be examined and assessed by an investigator at the renal outpatient department of the Royal London Hospital. Cardiac MRI will take place at the London Chest Hospital (aprox 20 min walk from RLH)

All assessments will be similar between the two groups. At each study point, participants will undergo the relevant assessment and will also receive one dose of the study drug to ensure compliance.

The table below details each study time point and exactly what will occur. Each Action is explained in more detail below.

| **Visit** | **Drug** | **Action** | **Action** | **Action** | **Action** | **Action** | **Action** | **Action** | **Action** | **Action** |
| --- | --- | --- | --- | --- | --- | --- | --- | --- | --- | --- |
| 0 weeks | Washout |  |  |  |  |  |  |  | Bloods | Examination |
| 2 weeks | n |  | Microcirc |  |  |  |  |  |  | Examination |
| 1 month (4 weeks) | y | ECG | Microcirc | SF 36 | Urine | MRI/echo | 24hr BP | USS neck | Bloods | Examination |
| 2 month | y |  | Microcirc |  | Urine |  |  |  | Bloods | Examination |
| 3 months | y |  |  |  |  |  |  |  | Bloods | Examination |
| 4 months | y |  | Microcirc |  | Urine |  |  |  | Bloods | Examination |
| 5 months | y |  |  |  |  |  |  |  | Bloods | Examination |
| 6 months | y |  |  |  |  |  |  |  | Bloods | Examination |
| 7 months | n | ECG | Microcirc | SF 36 | Urine | MRI/echo | 24hr BP | USS neck | Bloods | Examination |

**Time** – 0 weeks refers to recruitment, consent and enrolment. Randomisation will occur at month 1 (4 weeks after recruitment). The study will end at month 7 after recruitment. Patients will receive the study drug for 6 months in total.

**Drug** – at month 1 (week 4) patients will be randomized to and receive at that visit either placebo or ergocalciferol. Patients will receive all 9 capsules of study medication at this time. They will be required to take 1 dose weekly at home in the first month. Further study medication will be taken at subsequent clinic visits and patients will be observed swallowing their medication either by pharmacy staff or an investigator.

**ECG** – a 12 lead cardiac ECG will be undertaken. This is a painless, non-invasive procedure.

Duration 5 minutes.

**Microcirc** – This process involves four assessments of the microcirculation and will take place at a clinic visit in the same room.

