## Subject Population(s) for Analysis

We will recruit patients from the Royal London Hospital general nephrology outpatient clinics who match inclusion criteria as specified previously. Up to 40 patients in each arm will be recruited (80 in total). Patients will be provided with a full explanation of the purpose and details of the study and will receive a patient information sheet. Written informed consent will be obtained. Patients will undergo a screening evaluation to determine if they meet the study inclusion and exclusion criteria. This will include a medical history and physical examination as well as a review of all relevant existing blood tests.

Healthy volunteers will be recruited by advertisement to staff and students of Queen Mary, University of London and The Barts & the London NHS Trust and to the general community, as approved by a National Research Ethics Service (NRES) approved Research Ethics Committee.

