**NEW TEXT**

| **Visit** | **Drug** | **Action** | **Action** | **Action** | **Action** | **Action** |
| --- | --- | --- | --- | --- | --- | --- |
| 0 weeks | Washout |  |  |  | Bloods | Examination |
| 2 weeks | n | Microcirc |  |  |  | Examination |
| 1 month (4 weeks) | y | Microcirc | SF 36 | Urine | Bloods | Examination |
| 2 month | y | Microcirc |  | Urine | Bloods | Examination |
| 3 months | y |  |  |  | Bloods | Examination |
| 4 months | n | Microcirc | SF 36 | Urine | Bloods | Examination |

Each Action is listed in section 7 of the previous study protocol.

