**NEW TEXT**

**Drug** – at month 1 (week 4) patients will be randomized to and receive at that visit either placebo or ergocalciferol. Patients will receive all 6 capsules of study medication at this time. They will be required to take 1 dose weekly at home in the first month. Further study medication will be taken at subsequent clinic visits and patients will be observed swallowing their medication either by pharmacy staff or an investigator.

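### The 7-day pregnancy-test rule is not tied to a visit, and no test is placed at visit 3, where women are randomised and first dosed

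*Combined protocol and SAP*

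**What the plan says.** The text that follows the exclusion list in section 4.2 sets a recency rule: "Females of childbearing potential must have a negative pregnancy test within 7 days prior to being registered for protocol therapy". The term for the registration event appears nowhere else in the document.

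The recruitment text for subjects with CKD (section 4.3) gives the only timed test: "Female patients will be asked to undergo a pregnancy test at the time of the initial screening". The eligibility check is placed at the same stage. Section 4.3 says "Results of the screening evaluation will determine eligibility for entry into the study", and the section on subject populations for analysis says "Patients will undergo a screening evaluation to determine if they meet the study inclusion and exclusion criteria".

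The timeline is in Study Procedures and Schedule of Assessments: "0 weeks refers to recruitment, consent and enrolment", and "Randomisation will occur at month 1 (4 weeks after recruitment"). The Treatment Regimen section has the first capsule swallowed under observation at visit 3, after randomisation. Appendix 1 leaves the exclusion criteria unchanged and keeps this timing: "at month 1 (week 4) patients will be randomized to and receive at that visit either placebo or ergocalciferol". Its row for that visit reads "1 month (4 weeks) | y | Microcirc | SF 36 | Urine | Bloods | Examination". The main-trial row also includes urine and bloods. Neither row names a pregnancy test.

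**The concern.** A rule that a test be no more than 7 days old works only if staff know which event the 7 days count back from and when the test is to be done. Here the event is undefined, the only placed test is at or before week 0, and the first dose is at week 4. No re-check of eligibility at visit 3 is described. A team that follows the written procedures could therefore give the first capsule on a result four weeks old or more.

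Pregnancy is an exclusion criterion. The Clinical pharmacology text advises against vitamin D above the recommended daily amount in normal pregnancy unless the physician judges that benefit outweighs risk. Pregnancy is also a reason for withdrawal, on the separate ground that it would distort the microcirculatory measurements. Dosing is heaviest at the start: four weekly capsules of 50,000 IU (4 × 50,000 = 200,000 IU in the active arm) fall before visit 4, which also lists no test.

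**Working it through.** No sample size, power or alpha figure is involved. The check compares the eligibility rule with the procedures and counts days.

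**Inputs**
- Window: 7 days before registration (section 4.2).
- Placed test: initial screening, so at or before day 0 (section 4.3).
- Scheduled visits up to first dose: weeks 0, 2 and 4, that is days 0, 14 and 28 (main and Appendix 1 schedules).
- Randomisation and first dose: visit 3, day 28 (Treatment Regimen; Study Procedures; Appendix 1).
- Pregnancy tests in the schedules: none at any visit. The routine and additional blood lists contain none. The urine action covers sodium, calcium and protein:creatinine ratio only.

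**Reading 1: registration means randomisation (day 28)**
- Window: 28 − 7 = day 21, so days 21 to 28.
- Test on day 0: 28 days old, and 28 − 7 = 21 days too early. A test before week 0 is older still.
- Test at visit 2 (day 14): 28 − 14 = 14 days old, and 14 − 7 = 7 days too early.
- Visit 3 is the only scheduled visit inside the window.

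This is the more natural reading, because the rule refers to registration for therapy, week 0 is a washout visit, and no study drug is given before week 4. It remains an inference.

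**Reading 2: registration means enrolment at week 0**
- A test 0 to 7 days before day 0 satisfies the rule.
- Age at first dose: 28 + 0 = 28 to 28 + 7 = 35 days.

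**Expected exposure**

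The documents give no rates. Assume that 5% to 20% of patients are women of childbearing potential and that 0.5% to 2% of those conceive during the four-week run-in. Planned patients are 80 + 2 × 15 = 110, allocated 1:1, so half receive active drug.
- Low: 110 × 0.05 × 0.005 × 0.5 = 0.014 women.
- High: 110 × 0.20 × 0.02 × 0.5 = 0.22 women.

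Pregnancies missed at screening are not counted. In the other direction, a conception shortly before day 28 may not yet give a positive test, so a visit-3 test would prevent fewer exposures than these figures.

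**The case against.** The strongest reply is that the protocol is not contradictory. If registration is randomisation, section 4.2 already obliges staff to test on days 21 to 28, and the screening test is an extra check. If registration is enrolment, the two sections agree, and no passage sets a maximum age for the result at first dose. The schedules omit even the screening test that section 4.3 requires, so their silence about visit 3 is weak evidence. The case report form carries an eligibility checklist and may prompt a test. It and a procedures flowchart are listed as attachments but are not in the text available here. Investigators may also order tests on clinical grounds. The trial has one centre, contraception is required from consent, and the regimen is expected to stay well below toxic levels.

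Most of this stands. It establishes that the defect is an undefined term plus an omission, that it can be asserted only of the visible text, and that the risk is small. It does not close the gap. The screening test is at least placed in section 4.3, whereas nothing visible places one at visit 3. Following only the placed procedures leads to dosing on a result at least 28 days old. That either breaches the 7-day rule or leaves it with no force when the drug is given.

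**Conclusion.** The concern holds as a minor, precautionary safety point. On either reading, the only timed test is at least 28 days old at first dose. If registration means randomisation, that is at least 21 days outside the protocol's own limit.

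That the term is undefined and that no visit-3 test is placed is clear from the text. That registration means randomisation is the better reading but is not proven. Expected exposure is below one woman even at the top of the assumed range, and that range rests wholly on assumed rates. No demonstrated harm, bias or loss of power is claimed, and no analysis is affected.

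**What to change.** 1. In section 4.2, define registration for therapy as randomisation at visit 3.
2. In section 4.3, keep the screening test and state that it does not replace the visit-3 test.
3. In the 1-month row of both schedules, add a urine pregnancy test for women of childbearing potential (as section 4.2 already delimits them), done on the urine specimen collected on arrival.
4. Require the negative result to be recorded in the case report form before randomisation and before the first capsule.

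The cost is one definition, one sentence, one line in each of two tables, and one inexpensive test per eligible woman. No new visit or sample is needed. Reading the result before randomisation may add a short wait at visit 3.

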## Withdrawal of Subjects

### When and How to Withdraw Subjects

Withdrawal to occur if:

1. Pregnancy occurs during the trial (the CVS effects of pregnancy are likely to significantly alter the assessments of the microcirculation and therefore will invalidate study results)

2. Episode of symptomatic hypercalcaemia

3. Adverse reaction to any of the study drugs or procedures as judged by the principal investigator.

4. Patient request to withdraw for any reason

5. Permanent pace maker or other implantable cardiac device fitted during trial

6. Patients receive dialysis therapy during trial duration

7. Patients undergo kidney transplantation

8. Patients develop diabetes mellitus during trial duration

9. Failure to comply with study protocol, as judged by the principal investigator

- Intercurrent medical events and prescription of new medication by the patient’s general practitioner that are judged by the principal investigator not to interfere with the study protocol will not result in withdrawal. Such events will be recorded in the CRF.
- New patients will be recruited to ensure that the study meets the patient numbers in the power calculation
- If patients choose to withdraw or are withdrawn due to the criteria listed in 4.4.1 prior to completion of the study, they will be replaced unless they have withdrawn due to confirmed study drug toxicity.
- All patients who withdraw will be offered an appointment with their usual nephrologist after withdrawal to provide ongoing clinical care
- All withdrawals will be documented on the CRF and the patient’s general practitioner and usual nephrologist will be informed.

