### Data Collection and Follow-up for Withdrawn Subjects

We will use data and urine/blood samples which have already been collected for study analysis providing the patient gives consent for this to happen. Patients will have the opportunity and choice to inform the trial team how their health has been over the study duration even if they withdraw.

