# 7. Statistical Plan

## Sample Size Determination

This study is powered to detect a difference in microcirculatory function as assessed by iontophoresis. It is likely that if a difference is seen in microcirculatory function as assessed by iontophoresis that the other microcirculatory assessments will follow the same trend

We expect 85% failure in the placebo group and 50% failure in the intervention arm (35% difference in success). We have set alpha=0.05 and beta=0.1 which gives us 90% power.

Therefore:

n=[((15x85)+(50x50))/35^2]x10.5=32 patients in each arm

In order to ensure we achieve a total of 32 patients in each arm for an adequately powered study, we will recruit 40 patients per arm to allow for withdrawals and protocol violations.

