## Definition of Adverse Events

Adverse Event

An AE is any untoward medical occurrence in a subject to whom a medicinal product has been administered, including occurrences which are not necessarily caused by or related to that product. An AE can therefore be any unfavourable and unintended sign (including an abnormal laboratory finding), symptom or disease temporarily associated with the use of an Investigational Medicinal Product (IMP), whether or not considered related to the IMP. All such events during this trial will be recorded in the CRF.

Adverse Reaction (AR)

An AR is any untoward and unintended response in a subject to an Investigational Medicinal Product (IMP), which is related to any dose administered to that subject. All adverse events judged by either the reporting investigator or the Sponsor as having a reasonable causal relationship to a medicinal product qualify as adverse reactions. The expression reasonable causal relationship means to convey in general that there is evidence or argument to suggest a causal relationship.

Serious Adverse Event (SAE)

An SAE fulfils at least one of the following criteria:

- Is fatal – results in death (NOTE: death is an outcome, not an event)
- Is life-threatening
- Requires inpatient hospitalisation or prolongation of existing hospitalization
- Results in persistent or significant disability/incapacity
- Is a congenital anomaly/birth defect

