## Study Stopping Rules

Subjects who are withdrawn because of serious adverse events (including a Grade 3 or 4 toxicity (based on the Common Toxicity Criteria (CTC) version 3.0 – included with this document) will not be replaced. The Ethics Committee will be notified in writing of any study withdrawals that may occur as a result of toxicity.

The study will be stopped if there are any major safety concerns involving the patients involved in the trial as raised by the sponsor or the principal investigator. The study will end when the last patient has received the last dose of study medication and undergone the final assessments as in section 7.

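### Patients withdrawn after randomisation are replaced and not followed for outcomes, no analysis set is defined, and the replacement rules conflict

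*Combined protocol and SAP*

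**What the plan says.** **Withdrawal.** Section 4.4.1 lists nine reasons. They include symptomatic hypercalcaemia, adverse reaction, kidney transplantation, new diabetes, "Patients receive dialysis therapy during trial duration" and "Failure to comply with study protocol, as judged by the principal investigator". New medication leads to withdrawal only if the principal investigator judges that it interferes with the study (4.4.1; Prior and Concomitant Therapies).

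**Replacement.** The same section says of withdrawn patients that "they will be replaced unless they have withdrawn due to confirmed study drug toxicity", and adds that "New patients will be recruited to ensure that the study meets the patient numbers in the power calculation". It does not separate patients who leave before randomisation (visit 3, week 4) from those who leave after it.

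**Follow-up.** Section 4.4.2 says "We will use data and urine/blood samples which have already been collected for study analysis providing the patient gives consent for this to happen". Patients may also tell the team how their health has been, but no outcome assessment is scheduled after withdrawal.

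**Analysis.** Statistical Methods names a t test and gives no missing-data method. Subject Population(s) for Analysis describes recruitment, with up to 40 patients per arm, and defines no analysis set.

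**Other text on numbers.** Sample Size Determination needs 32 per arm and says "we will recruit 40 patients per arm to allow for withdrawals and protocol violations". Study Stopping Rules says that "Subjects who are withdrawn because of serious adverse events (including a Grade 3 or 4 toxicity" and similar cases will not be replaced, with no condition on cause.

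Appendix 1 leaves all other aspects of the protocol unchanged, so these rules also govern the additional study of 15 patients per arm.

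**The concern.** Randomisation protects the comparison only for the patients who were randomised. Replacement restores the count, but it does not restore the patients who left. If the reason for leaving is related to treatment or to the outcome, those who remain are a selected group, and replacements pass through the same filter.

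Two of the listed reasons plainly could be related. Hypercalcaemia is the main harm the protocol expects from ergocalciferol. A patient who starts dialysis leaves before the second of the two eGFR values (0 and 6 months) that measure progression of kidney disease, so a clear case of progression drops out of that endpoint.

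At stake are the end-of-treatment microcirculatory comparison and the eGFR comparison. Assessments that are not made at the time cannot be recovered at the analysis stage. Separately, staff cannot apply the replacement rules consistently as they stand.

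**Working it through.** **1. The plan's own figure.** From Sample Size Determination: [((15×85)+(50×50))/35²]×10.5 = (3775/1225)×10.5 = 32.36, stated as 32. This reproduces. Since 32/(1−0.20) = 40, the move to 40 per arm matches an implied 20% loss. The plan states no rate, and the allowance also covers protocol violations.

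**2. Replacement against the ceiling.** Number randomised per arm = target/(1−w), where w is an assumed withdrawal fraction.

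| w | target 40 completers | target 32 completers |
|---|---|---|
| 5% | 42.1 | 33.7 |
| 10% | 44.4 | 35.6 |
| 20% | 50 | 40 |

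Refilling 40 places breaks the ceiling of 40. Aiming for 32 completers stays within it, and the allowance then already does the work of replacement.

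**3. The conflict.** Take a patient admitted to hospital to start dialysis, unrelated to study drug, and withdrawn for it. Admission makes the event serious under the criterion "Requires inpatient hospitalisation or prolongation of existing hospitalization". Section 4.4.1 replaces this patient because there is no confirmed drug toxicity. Study Stopping Rules does not, because the withdrawal was for a serious adverse event.

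**4. How much selection could matter.** The documents give no input for this, so every setting below is an assumption. Outcomes are normal with SD 1, there is no treatment effect, and 40 are randomised per arm. Each patient has a propensity to leave with correlation ρ to the outcome, and the 8 most prone leave. The expected shift in that arm is ρ×φ(z₀.₂)/0.80 = ρ×0.280/0.80 = 0.35ρ, that is 0.175 SD at ρ = 0.5 and 0.245 SD at ρ = 0.7. Simulated results:

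| Scenario (8 removed per arm) | Bias (SD) | Type I error |
|---|---|---|
| Same mechanism in both arms | about 0 | 5–6% |
| 2 of 8 outcome-related, one arm, ρ = 0.5 | 0.05 | 5–6% |
| 4 of 8 outcome-related, one arm, ρ = 0.5 | 0.09 | about 7% |
| ρ = 0.5 in one arm, 0.3 in the other | 0.07 | 6–7% |
| All 8, one arm only, ρ = 0.3 | 0.10 | 7% |
| All 8, one arm only, ρ = 0.5 | 0.17 | 10–11% |
| All 8, one arm only, ρ = 0.7 | 0.24 | 18% |

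In the last two rows, replacing up to 40 completers leaves the bias unchanged and raises type I error to 12–13% and 21%, because the biased difference is estimated more precisely.

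On the plan's binary scale, suppose only non-responders leave, only from the active arm, and are replaced to 40. The observed success rate becomes p/(1−w).

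- True success 15% in both arms: 0.15/0.90 = 16.7% and 0.15/0.80 = 18.8%. The spurious differences are 1.7 and 3.8 points, with type I error 5.5% and 7.3%.
- True success 50% in both arms (assumed): the differences are 5.6 and 12.5 points, with type I error 7.8% and 20.1%.

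**5. The price of analysing everyone.** Assume withdrawn active patients have the placebo success rate of 15%, so active success is 0.50(1−w)+0.15w. This gives 46.5% at w = 10% and 43.0% at w = 20%. With 40 per arm, power by the pooled two-proportion test is 93.2% at w = 0, 87.8% at 10% and 80.0% at 20%. The plan's own unpooled formula, which is slightly more favourable, needs 40 and 50 per arm for 90% power at 10% and 20%.

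**The case against.** The best defence is that the plan limits differential removal. Investigators and patients are blinded, so non-compliance is judged without knowledge of the arm. Raised calcium without symptoms leads to an omitted dose, not withdrawal. Appendix 1 reports no laboratory-confirmed hypercalcaemia so far. Patients expected to need dialysis within 6 months are excluded. All of this stands, and it makes the high end of the table unlikely. It does not remove the route: blinding cannot prevent selection by events that the treatment itself causes, patients admitted with hypercalcaemia are unblinded, and starting renal replacement therapy is listed as an expected event.

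Some stronger readings are tempting, and the documents do not support them.

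- A reader might infer that the plan declares a completer analysis. It names no analysis set, and section 4.4.2 lets earlier visits be used with consent (microcirculation is also measured at months 2 and 4). The completer character follows in effect, and for the end-of-treatment values only.
- A reader might infer that withdrawals are certainly counted twice, once in the 40 and again by replacement. Step 2 shows a reading in which both fit within 40. The text is ambiguous.
- A reader might infer that any new medication ends participation, or that dialysis removes all patients who progress. Neither is so: medication is judged case by case, and patients who progress without dialysis stay in.

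**Conclusion.** The point holds. Following the written rules after randomisation can bias the end-of-treatment comparison, and nothing in the analysis sections counters it. Replacing patients who leave before randomisation is harmless, but section 4.4.1 does not draw that line.

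That bias exists, or differs by arm, is a risk and not a demonstrated fact. Its size and direction cannot be derived from the documents. Under the assumed 8 of 40 removed per arm, type I error lies between about 5% and 18%. Values of 10% or more arise only when all removals are outcome-related in one arm and none in the other, with correlation 0.5 to 0.7.

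The conflict between section 4.4.1 and Study Stopping Rules needs no assumption. The ceiling of 40 per arm adds an ambiguity that must be settled at the same time. None of this makes the stated sample size of 32 wrong. The issue should be fixed in the protocol, because outcome data that are not collected cannot be supplied later.

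**What to change.** 1. State that the primary analysis includes all randomised patients in their assigned arm, with a stated method for missing values and a per-protocol analysis as sensitivity.
2. Separate stopping study drug from leaving the study. Unless consent is withdrawn, still request the scheduled outcome assessments that remain feasible and safe: visits 6 and 9 in the main study, visit 6 in the Appendix 1 study. MRI would not be requested where a cardiac device has been fitted.
3. Allow replacement only for patients who leave before randomisation at visit 3.
4. Reconcile section 4.4.1, Study Stopping Rules and the ceiling in Subject Population(s) for Analysis, and say whether 40 per arm counts patients randomised or patients completing.
5. Keep patients who start dialysis or receive a transplant in the kidney analysis, at least through a sensitivity analysis that counts them as progressed. The eGFR endpoint itself need not change.

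When study drug is stopped remains a clinical decision and is not altered here.

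The cost is protocol and analysis-plan wording, plus visits that are already scheduled, for patients who are off drug. There is a real statistical price in dilution (step 5 of the working). The protocol should state the assumed withdrawal rate and the power that goes with it.
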